#### Pylorus dilatation/EPBD

All patients will routinely receive a gastroscopy the day before surgery to confirm intraluminal tumor extent and exact location after possible neoadjuvant treatment. After neoadjuvant treatment tumor size and consequently surgical strategy could change. Therefore, it is essential that a patient consultation after endoscopy and before surgery is possible. The gastroscopy is performed under analgosedation with propofol. In patients randomized to the PDG, a 2-min balloon dilatation of the pylorus with a 20-mm balloon (Boston Scientific, Ireland) will be performed. This dilatation is performed through the scope by water insufflation with a pressure of 608 kPa. Patients randomized to the NPDG receive staging endoscopy without pylorus dilatation. If—due to any reason (e.g., stenotic tumor)—balloon dilatation is not possible, it will not be carried out during the preoperative gastroscopy. The patient can request to terminate the study participation at any time. The intervention is proven to be a feasible and safe and part of the clinical routine in all participating centers. The study will impose no additional risk for the included patients.

#### Placebo intervention

The placebo intervention is the gastroscopy without performing EPBD. The pylorus is passed by the endoscope as it is in the intervention group. Gastroscopy 1 day preoperatively is primarily used for restaging and surgical planning. Therefore, no unnecessary examination is carried out in the placebo group.

During the intervention, the patients are sedated. After dilatation, there are no scars or visible changes, nor can the patient sense the difference between the intervention and an ordinary endoscopy. The only possibility for the patients to discover their group allocation might be the duration of the intervention. However, we do not believe medical laypersons to have those insights.

#### Surgery and perioperative management

All patients undergo a minimally invasive esophagectomy with 2-field lymphadenectomy and Ivor-Lewis reconstruction. This includes formation of a gastric conduit and creation of a transthoracic esophagogastrostomy using a circular stapler, as previously described [17, 18]. In order to avoid bias by inhomogeneous treatment pathways and surgical procedures, we ensure all participating centers perform the minimally invasive esophagectomy according to the published papers. All participating surgeons were trained at University Hospital Mainz and routinely apply the same surgical procedure.

The perioperative management in both groups is equal. Postoperative oral food intake is routinely initiated on the third postoperative day, beginning with water in sips. Thereafter, oral intake is increased with sieved food on the fourth and solid food on the fifth postoperative day.

### Statistical analysis

#### Exclusion to primary analysis

The analysis of the primary endpoint will be performed in accordance with the intention to treat principle. First, an intention-to-treat analysis will be carried out, which involves all patients randomized into the study. Second, a modified per-protocol analysis with following patients excluded will be performed:Endoscopically not passable tumors in the staging endoscopy 1 day before surgery (no intervention possible)Initiation of oral food intake later than 10 days postoperatively due to any reason apart from pyloric dysfunctionAnastomotic leakage at a time when oral food intake is not completed or 10 days after initiation of oral food intake has not passed.

Patients fulfilling the above-mentioned criteria cannot be evaluated properly regarding the occurrence of postoperative DGE or pyloric dysfunction. Since DGE does not affect anastomotic leakage rates, a bias towards less DGE in the primary analysis due to the exclusion of patients with anastomotic leakage is not likely [19]. However, anastomotic leakages interrupt the regular course of oral food intake, and its influence on the gastric conduit remains unclear. Therefore, a modified per-protocol analysis will be carried out with the patients not excluded from the primary analysis.

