### Primary and secondary endpoints

The primary endpoint of the PROPPER trial is the occurrence rate of pyloric dysfunction. Pyloric dysfunction is diagnosed if one of the following symptoms appears during the first 14 days after surgery:One-time vomiting of either liquid or sieved food during gradual return to oral food intakeRecurrent vomiting of solid food during gradual return to oral food intakePerformed EPBD independent of vomiting or oral food intake for other reasons

(Oral food intake has to be initiated latest 10 days after surgery to evaluate postoperative pyloric dysfunction.)

This definition was elected since vomiting during the process of returning to oral food intake after esophagectomy is the one clinical parameter that indicates pyloric dysfunction. However, clinical experience shows that one-time vomiting after solid food intake happens occasionally after overeating and dietary errors. Therefore, vomiting after solid food intake must happen repeatedly to count as pyloric dysfunction. In all participating centers, postoperative vomiting, as defined above, triggers performing endoscopy and EPBD.

The timing of 14 days after surgery was chosen in accordance with the international expert consensus based on a modified Delphi process published in 2020 [16]. DGE that occurs within 14 days after the surgery was defined as early DGE. We suspect early DGE to be affected most by preoperative EPBD since the time between intervention and outcome is short, and after weeks or months, additional disturbance variables such as other complications might add bias to our results.

The primary outcome is assessed by study nurses responsible for data acquisition. They will interview the patients about any vomiting after the surgery. Thereby, we ensure to receive honest answers and capture patient experience.

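### The per-protocol leak exclusion can run past day 14, when the primary endpoint has already closed, and so remove patients whose outcome is fully observed

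*Protocol article*

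**What the plan says.** Three parts of the protocol article bear on this.

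- **Endpoint** (Primary and secondary endpoints): "Pyloric dysfunction is diagnosed if one of the following symptoms appears during the first 14 days after surgery". The same section adds that "Oral food intake has to be initiated latest 10 days after surgery to evaluate postoperative pyloric dysfunction".
- **Routine feeding** (Surgery and perioperative management): "Postoperative oral food intake is routinely initiated on the third postoperative day, beginning with water in sips", after which "oral intake is increased with sieved food on the fourth and solid food on the fifth postoperative day".
- **Analysis sets** (Exclusion to primary analysis): first "an intention-to-treat analysis will be carried out, which involves all patients randomized into the study". A modified per-protocol analysis follows. One of its exclusions is a leak that occurs before oral intake is completed or while "10 days after initiation of oral food intake has not passed". The reason given for the exclusions is that these patients "cannot be evaluated properly regarding the occurrence of postoperative DGE or pyloric dysfunction".

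**The concern.** The endpoint clock starts at surgery and the leak-exclusion clock starts at feeding. Nothing in the article ties the end of one to the end of the other. When feeding starts late enough, the exclusion window is still open after the endpoint window has shut. A leak at that point cannot change whether the patient had pyloric dysfunction by day 14, yet it takes the patient out of the analysis set.

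Two things are at stake. The stated rationale fails for these patients, because their outcome has been observed in full. And membership of the modified per-protocol set then depends on something that happens after the outcome is decided, which an analysis set should avoid. At the least this wastes patients in a trial of 118. If late feeding or late leakage were related to arm or outcome, it could also distort the comparison in that set.

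**Working it through.** The plan states no figure on this point, so there is none to reproduce. The check is day arithmetic on the plan's own rules.

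**Inputs**
- Endpoint closes on postoperative day 14 (Primary and secondary endpoints).
- Routine start of oral intake: day 3. Latest start still regarded as evaluable: day 10 (Surgery and perioperative management; Primary and secondary endpoints).
- Leak exclusion, 10-day clause: open until 10 days after the start of oral intake (Exclusion to primary analysis).

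**Formulas.** For a feeding start on day *s*:
- end of the exclusion window = *s* + 10
- overhang = (*s* + 10) − 14 = *s* − 4

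| Feeding start *s* | Exclusion window ends | Relative to day 14 |
|---|---|---|
| Day 3 (routine) | Day 13 | 1 day before |
| Day 4 | Day 14 | same day |
| Day 5 | Day 15 | 1 day after |
| Day 6 | Day 16 | 2 days after |
| Day 7 | Day 17 | 3 days after |
| Day 8 | Day 18 | 4 days after |
| Day 9 | Day 19 | 5 days after |
| Day 10 | Day 20 | 6 days after |

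The windows end together only for a day-4 start.

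**Example.** Feeding starts on day 8 and a leak is found on day 16. The endpoint closed on day 14. The exclusion window runs to day 18, so the patient is dropped with a complete outcome.

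**Day-count convention.** The table counts a leak on day *s* + 10 as inside the window. If it is counted as outside, the last excluded day is *s* + 9. The overhang then begins with a day-6 start and reaches day 19 for a day-10 start. The conclusion is the same.

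**The other clause.** The exclusion also applies while oral intake is not completed, and the article does not define completion. This clause has no fixed end day, so it could reach past day 14 for any feeding start. A day-14 cap has to cover both clauses.

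**The case against.** **It concerns a secondary analysis.** This stands. Intention-to-treat comes first and includes all randomized patients. The section heading speaks of exclusion to the primary analysis, and a reader might infer that the main result is affected. The order set out in the text does not support that.

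**It does not arise on the routine pathway.** This stands for the 10-day clause. With a day-3 start the window ends on day 13. An overhang through that clause needs both a start on day 5 or later and a leak after day 14 but within 10 days of starting.

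**Late starters have too little time at risk.** A reader might infer that the mismatch leaves a day-10 starter with only 14 − 10 = 4 days of observation and lowers the event rate. The 4 days follow from the endpoint window and the day-10 limit alone, so changing the leak rule would not lengthen them. They apply only to the vomiting components, because dilatation counts whatever the oral intake. Nor can the loss be sized from the planning rate: the Introduction says that the 37.5% in the retrospective study was measured by required postoperative dilatation, not by vomiting over a known feeding period. Treating staff are unblinded, but the article says that perioperative management is equal in both groups, and nothing in it shows that feeding starts differ by arm.

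**The rule discards observed events.** It does remove a patient who met the endpoint and then leaked. It is tempting to keep such patients and drop only leakers without an event. That would select on outcome, because every retained leaker up to day 14 would then be an event. To illustrate, assume that 10% leak by day 14, independently of pyloric dysfunction, and that half of the leakers' events precede the leak. A true rate *p* becomes 0.95*p* / (0.90 + 0.05*p*):
- control: 0.35625 / 0.91875 = 38.8%, against 37.5%
- dilatation: 0.1254 / 0.9066 = 13.8%, against 13.2%

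The difference widens from 24.3 to about 24.9 points. Excluding leakers whatever their outcome avoids this. It also fits the plan's argument that delayed emptying does not affect leakage.

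That argument does not, however, justify excluding someone for a leak after day 14, when the outcome is already complete.

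**Conclusion.** The point holds in a narrow form. The leak exclusion is anchored to feeding and the endpoint to surgery. For feeding that starts on days 5 to 10, the exclusion stays open 1 to 6 days beyond the endpoint, to days 15 to 20. In that interval it removes fully observed patients, contrary to its own rationale.

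The consequence is confined to the modified per-protocol set. It does not arise through the 10-day clause on the routine day-3 start. The number of patients affected cannot be estimated, because the article gives no leak rate, no timing of leaks and no distribution of feeding starts. No bias in a known direction is shown. This is a correction of a stated rule that costs nothing, not a threat to the primary result.

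**What to change.** In the section on exclusion to primary analysis, limit the leakage criterion to leaks on or before postoperative day 14. Apply the cap to both clauses (intake not completed, and 10 days from the start of intake). Apply the criterion regardless of whether the patient has already met the endpoint. The 14-day endpoint window, the feeding pathway and the intention-to-treat analysis stay as they are.

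The cost is one phrase, with no new data and no change in sample size. It should be made before outcome data are examined, including at the interim analysis, so that it cannot look data-driven.

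A supportive analysis that counts pyloric dysfunction up to 10 days after the start of oral intake is optional. It is possible only if dates of feeding start and of events are recorded. The schedule table marks delayed gastric emptying at visits up to 3 months, but the article does not say that event dates are collected.

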### Data analysis

The statistical analysis will be performed using the statistical program SPSS (IBM). Both an intention-to-treat analysis and per-protocol analysis are planned. Primary and secondary outcomes will be compared using the chi-squared test, Fisher exact test for categorical variables, and Mann–Whitney *U* test for non-parametric variables. Mortality will be compared using Kaplan–Meier curves and log-rank test. The pain scales will be analyzed using mixed linear models, quality of life by using an analysis of covariance.

There will be an interim analysis after 75% of the participants were monitored for the occurrence of the primary endpoint. If the hypothesis is confirmed or reaching statistical significance is impossible at that point, the study will be ended.

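### The protocol defines the primary analysis as intention-to-treat in all randomised patients, yet describes the same primary analysis as excluding patients, so the analysis that decides the trial is contradictory

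*Protocol article*

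**What the plan says.** In the protocol article, the section *Exclusion to primary analysis* opens with a clear rule: "The analysis of the primary endpoint will be performed in accordance with the intention to treat principle". It then gives an order, beginning with everyone randomised: "First, an intention-to-treat analysis will be carried out, which involves all patients randomized into the study". The next analysis in that order is the one that carries the exclusions: "Second, a modified per-protocol analysis with following patients excluded will be performed". It has three criteria: a tumour that the endoscope cannot pass on the day before surgery, oral intake starting after day 10 for a reason other than pyloric dysfunction, and a leak of the anastomosis, defined as "leakage at a time when oral food intake is not completed or 10 days after initiation of oral food intake has not passed".

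Three places in that section attach the exclusions to the primary analysis instead:
- the section heading;
- the reassurance that "a bias towards less DGE in the primary analysis due to the exclusion of patients with anastomotic leakage is not likely";
- the last sentence, which describes the per-protocol set as the patients who were not excluded from the primary analysis.

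Elsewhere, *Data analysis* says only that "Both an intention-to-treat analysis and per-protocol analysis are planned", and ends the trial at interim if the hypothesis is confirmed or significance is out of reach. *Sample size calculation* leaves that decision to the principal investigator. Neither section says which analysis set is used. *Primary and secondary endpoints* adds: "Oral food intake has to be initiated latest 10 days after surgery to evaluate postoperative pyloric dysfunction".

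**The concern.** An analysis of everyone randomised excludes nobody. A section that first defines such an analysis as primary and then defends the exclusions made in it leaves two answers to one question: which result decides the trial? The same gap carries over to the interim stop.

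The choice matters because of when the exclusions arise. *Randomization and blinding methods* places randomisation in the outpatient department, and all three criteria are met later. Late intake and leakage also come after the dilatation or sham, so they can in principle be related to treatment and to outcome. A primary analysis that dropped these patients would no longer compare the groups as randomised.

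The leak criterion has a further problem: it can remove a patient whose endpoint event has already been recorded.

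**Working it through.** **1. The statements side by side**

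| Place | Who is in the primary analysis |
|---|---|
| Opening sentences of *Exclusion to primary analysis* | All randomised patients |
| Heading of that section | Some are excluded |
| Sentence on bias | Leak patients are excluded |
| Last sentence | Patients meeting any of the three criteria are excluded |
| *Data analysis* | Both sets analysed; neither named as deciding |
| Interim rule (*Sample size calculation*, *Data analysis*) | Not stated |

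The bias sentence mentions leakage only. The extension to late intake and non-passable tumours rests on the heading and the last sentence.

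**2. Timing of the leak criterion**

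*Surgery and perioperative management* starts intake on day 3, with sieved food on day 4. The criterion's window then runs to day 3 + 10 = 13. A patient who vomits sieved food on day 4 has met the endpoint. A leak on day 8 still removes that patient from the per-protocol set. If intake starts after day 4, the window extends past the 14-day endpoint. At the latest permitted start it ends on day 10 + 10 = 20.

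**3. The plan's own sample size**

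Inputs from *Sample size calculation*: 13.2% against 37.5%, two-sided 5%, power 0.80. The pooled two-proportion formula gives 50 per arm, against 49 stated; its power at 49 is 0.799. The stated figure is reproduced. The 59 per arm is 49 × 1.2 = 58.8, rounded up.

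**4. Power by analysis set**

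The share of patients meeting the exclusion criteria is not given. The 20% used below is an assumption, borrowed from the dropout allowance. Power is exact for the chi-squared test.

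- ITT, 59 per arm, planned rates in everyone: 0.880 (normal approximation 0.868).
- ITT, 59 per arm, 20% of each arm unable to have an event: 0.132 × 0.8 = 0.106 and 0.375 × 0.8 = 0.300, power 0.776 (normal approximation 0.754).
- Exclusion set: 59 × 0.8 = 47.2, so 47 per arm at the planned rates, power 0.791 (normal approximation 0.782).

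With other assumed shares, by the normal approximation: at 10%, ITT with those patients as non-events has 0.82 and the exclusion set 0.83; at 30%, 0.68 and 0.73.

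**5. False-positive chance if either analysis could be used**

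Simulation of 400,000 trials per scenario with no treatment effect, event rates of 20%, 25% and 30%, ITT at 59 per arm and the exclusion set at 47 per arm:

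- Excluded patients have the same event rate as the rest: at least one analysis is significant in 7.2% to 7.4% of trials, against about 5% for one analysis.
- Excluded patients are all counted as non-events: 4.9% to 5.1%, which is no inflation.

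**The case against.** The best case for the plan is that its governing text leans one way. ITT is named as the principle for the primary endpoint and comes first. The list of exclusions hangs grammatically on the second analysis, and *Data analysis* also puts ITT first. On this reading, the later references to a primary analysis are loose wording for analysis of the primary endpoint. That is plausible, and it is probably what was meant. It still requires setting aside a heading and two sentences, one of which argues that excluding leak patients will not bias the primary analysis. That argument would be unnecessary if the primary analysis excluded nobody. This is a conflict in the text as it stands, not detail left to an analysis plan.

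Several stronger readings are tempting, and the documents do not support them:

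- **Patients who never eat are scored as non-events.** No section says so. *Missing data* names multiple imputation if a method is needed, and the third endpoint component, a performed EPBD, does not depend on eating.
- **Staff who know the allocation decide the exclusions.** Treating personnel are unblinded, but the study nurses who collect outcomes are not told the allocation, and no section says who applies the criteria.
- **The 20% dropout allowance fits only an analysis that drops patients.** The protocol does not say what dropout comprises, and withdrawal is allowed.
- **ITT power is as low as 67%.** That figure follows from 0.132 × 0.8 + 0.375 × 0.2 = 0.181 against 0.375. It assigns the whole 20% to undilated patients in the EPBD arm, although known stenosis is an exclusion criterion and no rate of non-passable tumours is given.

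**Conclusion.** The contradiction is real and concerns the analysis that decides the trial, both at the interim and at the end. It rests on the wording alone and needs no assumption. It should be resolved before the interim analysis.

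Its numerical size is not fixed by the documents. ITT power of 88% holds if the planned rates apply to everyone randomised; about 78% holds if 20% cannot have an event. A reader might infer that the error rate is inflated to about 7.3%. That holds only if the excluded 20% are a random subset with the same event rate as the others and success could be claimed from either analysis. The protocol states neither, and the inflation disappears if the excluded patients are all counted as non-events. What stands without figures is that an exclusion-based primary analysis would give up the protection of randomisation, and that the leak criterion can discard observed events.

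**What to change.** - State that the ITT analysis of all randomised patients, in the arm to which they were randomised, is the only confirmatory analysis at interim and final, and that the modified per-protocol analysis is supportive.
- Retitle the section *Exclusions from the per-protocol analysis*, and correct the bias sentence and the last sentence so that they refer to that analysis.
- In the ITT set, count any endpoint component observed by day 14 as an event, and apply the multiple imputation already named under *Missing data* to patients who never become evaluable.
- Do not repair the leak criterion by excluding a leak only when it precedes an endpoint event. Leak patients with an earlier event would stay and those without would go, so membership would depend on the outcome.

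The cost is protocol wording and the imputation analysis; no further patients are needed. The downside is that the ITT estimate may be smaller than the per-protocol one.

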#### Sample size calculation

The hypothesis of this study is a lower rate of pyloric dysfunction in patients receiving preoperative EPBD compared to a control group receiving a sham intervention. In order to assess a sample size, the rates of pyloric dysfunction of the retrospective study of Hadzijusufovic et al. were used, since operative techniques and perioperative treatment pathways do not differ from those used in the PROPPER trial. In this study, the pyloric dysfunction rate in the PDG was 24.3% lower than in the NPDG (13.2% vs. 37.5%). With a two-sided 5% significance level, 49 patients per arm will be needed to achieve a power of 0.8 to detect a difference. Compensating for a dropout rate of approximately 20%, a sample size of 118 patients with 59 patients in every study arm will be needed. After 89 patients, an interim analysis will be carried out. The study will be terminated if the superiority of the EPBD intervention has already been proven or cannot be proven at all. Otherwise, recruitment will be carried on until 118 patients are included. This will be decided by the principal investigator (PI).

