**Methods:**

This study is designed as a multicenter randomized controlled trial (RCT) including patients with esophageal cancer or cancer of the gastroesophageal junction (adenocarcinoma and squamous cell carcinoma, with or without neoadjuvant treatment) scheduled for minimally invasive esophagectomy with gastric pull-up. After randomization, patients will either receive preoperative EPBD or a sham intervention in the routine preoperative endoscopy performed 1 day before surgery. The primary endpoint of this study will be rates of DGE, particularly those resulting from pyloric dysfunction, requiring intervention. Secondary outcomes will be major and minor postoperative complication rates, in-hospital mortality, adverse events during gastroscopy, length of ICU and hospital stay as well as postoperative pain and quality of life. In order to detect a difference between both groups at a two-sided 5% significance level, to achieve a power of 0.8 with a calculated dropout rate of approximately 20%, a sample size of 118 patients with 59 patients in every study arm will be needed.

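### The 59 patients per arm do not follow from 49 per arm and a 20% dropout rate: they cover a loss of about 17%, and 20% would need 62 per arm

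*Protocol article*

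**What the plan says.** The protocol article, section Sample size calculation, takes the pyloric dysfunction rates of 13.2% (dilatation) and 37.5% (no dilatation) from the earlier retrospective study. It derives the number before dropout: "With a two-sided 5% significance level, 49 patients per arm will be needed to achieve a power of 0.8 to detect a difference". The next sentence inflates it: "Compensating for a dropout rate of approximately 20%, a sample size of 118 patients with 59 patients in every study arm will be needed". The Methods part of the abstract gives the same total with the same rate: "to achieve a power of 0.8 with a calculated dropout rate of approximately 20%, a sample size of 118 patients". No inflation formula is stated in either place.

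Three other sections bear on who is lost. Exclusion to primary analysis puts an intention-to-treat analysis of all randomized patients first. A modified per-protocol analysis comes second and removes patients with an impassable tumour, late oral intake or an anastomotic leak. Missing data names multiple imputation, if a method is needed. Data analysis names the tests: "Primary and secondary outcomes will be compared using the chi-squared test, Fisher exact test for categorical variables".

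**The concern.** Three stated figures must fit together: 49 evaluable per arm, a 20% loss and 59 enrolled per arm. They do not, because 20% of 59 is 11.8 patients and 59 − 11.8 = 47.2, which is below 49. The plan itself gives 49 as the number needed for its power.

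At stake is whether the sample size statement is accurate, in the section that justifies the trial's size and in the abstract, which most readers will rely on. Someone who reads 20% will take it that the trial can lose one patient in five and keep its planned power.

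**Working it through.** **Inputs** (Sample size calculation): rates p1 = 0.375 and p2 = 0.132, difference 0.243; two-sided 5% level; power 0.8; equal arms; dropout about 20%.

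**Step 1. Reproduce the 49.** The two-proportion formula with pooled variance under the null hypothesis is

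n = [1.96·√(2·p̄(1 − p̄)) + 0.8416·√(p1(1 − p1) + p2(1 − p2))]² / (p1 − p2)²

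- p̄ = (0.375 + 0.132)/2 = 0.2535, so √(2 × 0.2535 × 0.7465) = 0.6152.
- √(0.2344 + 0.1146) = 0.5907.
- n = (1.2058 + 0.4972)² / 0.0590 = 49.1 per arm.

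The plan's 49 is reproduced. Strict rounding up gives 50, and power at 49 is 79.9%, so 49 has no slack. Other formulas give somewhat fewer patients: 46.4 with unpooled variance and 47.6 with the arcsine transformation.

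**Step 2. Apply the dropout rate.**

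- Adding 20% to the evaluable number: 49 × 1.2 = 58.8, rounded up to 59. This is exactly the stated figure.
- Dividing by the share retained: 49/(1 − 0.20) = 61.25, rounded up to 62 per arm, or 124 in total.

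Only the second leaves 49 after a 20% loss. The gap is 3 per arm and 6 in total (6/118 = 5%).

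**Step 3. What 59 per arm can absorb.** 1 − 49/59 = 10/59 = 16.9%.

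**Step 4. Power for the number actually analysed** (13.2% versus 37.5%, two-sided 5%):

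| Analysed per arm | Pooled normal formula | Exact power, uncorrected chi-squared |
|---|---|---|
| 47 (59 less 20%) | 78.2% | 79.1% |
| 49 (plan's target) | 79.9% | 81.0% |
| 59 (no loss) | 86.8% | 88.0% |

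A true 20% loss from 59 therefore costs 79.9 − 78.2 = 1.7 points against the plan's own target of 49, and leaves power 1.8 points below 80%. At 47 per arm the arcsine formula gives 79.5% and the unpooled formula 80.5%.

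**The case against.** Four points can be made for the plan as written.

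- **The rate is approximate.** Both statements say so, and 59 covers 16.9%. This softens the point but does not remove it. The reader is given 20% as the planning value, and at 20% the design falls short of its own 49. Ten extra patients are about 20% of 49, but a dropout rate is a share of those enrolled.
- **The main analysis need not lose anyone.** The first analysis is by intention to treat on all randomized patients, with imputation if needed, and the endpoint falls within 14 days of surgery. This stands. The 47 per arm describes a complete-case analysis or the modified per-protocol set. The 87% at 59 per arm is an upper bound, because imputed outcomes carry less information than observed ones.
- **The power effect is small and depends on the formula.** This stands too. By the unpooled formula 47 per arm is enough, although that formula does not return the plan's 49.
- **The multiplication by 1.2 is inferred.** The match is exact, but the article states no formula. The inconsistency holds however 59 was reached.

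A reader might infer that the trial is materially underpowered or fails to reach its 80%. The documents do not support that: the shortfall is under 2 points, arises only if a full 20% leave the analysis, and disappears under one common formula.

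A reader might also cite Fisher's exact test, with power of 71.9% at 47 per arm. Most of that drop comes from the test, since power with Fisher's test is already 74.3% at 49. The article lists both tests without assigning Fisher's to the primary endpoint. That is a separate question and does not measure the dropout error.

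**Conclusion.** The stated dropout allowance does not follow from the plan's own figures. With 49 evaluable per arm and 20% dropout the number is 62 per arm (124 in total), against the stated 59 (118), which allow for about 17%.

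The consequence is minor. If 20% leave the analysis, power is about 78% by the pooled formula or 79% by exact calculation for the uncorrected chi-squared test. If all 59 per arm contribute observed outcomes, it is about 87%. These values assume the plan's rates of 13.2% and 37.5%, equal loss in both arms and a single two-sided test at 5%. The endpoint, the analysis and the validity of the comparison are untouched.

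**What to change.** Change the sentence in Sample size calculation and the matching one in the abstract to one of these two forms:

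- 118 patients (59 per arm) allow for about 17% dropout at about 80% power; or
- with 118 patients and 20% dropout, about 47 per arm remain and power is about 78%.

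It would help to add the inflation formula and to say which analysis set the dropout refers to. Either form is a text correction that adds no patients; the only cost is a slightly less favourable figure. If the sponsor prefers to keep both 20% and 49 evaluable per arm, the total is 124, and the interim look, now at 89 patients (75% of 118 = 88.5), would have to be restated (75% of 124 = 93).
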